**STUDY SUMMARY**

**Purpose:** To conduct an individual participant data (IPD) meta-analysis of prospective HIV prevention studies to evaluate prevalence and incidence of sexually transmitted infections (STIs) and bacterial vaginosis (BV) among women in sub-Saharan Africa

**Design:** Meta-analysis of individual participant data from 18 prospective HIV prevention studies using both one- and two-stage meta-analysis approaches.

**Study Population:** Approximately 37,000 women from clinic and community populations and groups of women at high-risk of HIV infection enrolled in selected prospective studies in sub-Saharan Africa.

**Primary Objectives:** 1) To evaluate the prevalence of selected

STIs/BV among women in sub-Saharan Africa by region, population type, and other pre-specified characteristics.

2) To evaluate the incidence of selected

STIs among women in sub-Saharan Africa by region, population type, and other pre-specified characteristics.

**Secondary Objectives:** 1) To evaluate the prevalence and incidence of co-

infections among the STIs/BV.

**LIST OF ABBREVIATIONS AND ACRONYMS**

BV bacterial vaginosis

CDC Centers for Disease Control and Prevention

EDCTP European and Developing Countries Clinical Trials Partnership

EIA enzyme immunoassay

HC-HIV Hormonal Contraception and Risk of HIV Acquisition

HIV human immunodeficiency virus

HPV human papillomavirus

HSV-2 herpes simplex virus type 2

IPD individual-participant data

RCT randomized controlled trial

RPR rapid plasma reagin

STI sexually transmitted infection

STROBE strengthening the reporting of observational studies in epidemiology

TPHA *Treponema pallidum* hemagglutination assay

TPPA *Treponema pallidum* particle agglutination assay

VPRP Vaginal Practices Research Partnership

WHO World Health Organization

**1. BACKGROUND**

Sexually transmitted infections (STIs) and bacterial vaginosis (BV) are widespread globally. These conditions result in a range of sexual, reproductive and maternal-child health consequences, including genital symptoms, pregnancy complications, infertility, enhanced HIV transmission, anogenital cancers, and important psychosocial consequences. The World Health Organization (WHO) estimates that 357 million new curable STIs (gonorrhea, chlamydia, syphilis, and trichomoniasis) occurred globally [2] and 417 million people had herpes simplex virus type 2 (HSV-2) infection during 2012 [3]. However, the paucity of high-quality published STI prevalence studies, especially among general populations and for low-income countries, including the lack of data from most African countries, has limited the accuracy of the estimation process. When studies do exist, they are often small and involve different analytic methods, making their use problematic for summary estimates. Global estimates of BV occurrence are not available.

In 2013, WHO held a technical consultation on accelerating development of effective new STI vaccines, which resulted in a global roadmap for STI vaccine development [4]. The roadmap outlines the critical need for better data on the burden of STI infection in low-income countries to more accurately assess the potential impact of STI vaccines, to stimulate investment in vaccine development, and to guide future vaccine implementation and evaluation. In addition, global STI management guidelines are currently being updated [5], and key decisions about the use of syndromic management (the use of presumptive treatment for symptomatic people without the use of laboratory tests) are dependent on accurate STI and BV prevalence data in different settings. Another consultation was held in 2013 on Methods for Improved Global STI Estimates. Technical experts from this meeting also identified the need for additional estimates and highlighted the importance of exploring potential data available through clinical research trials networks to improve estimates.

In 2014, in collaboration with investigators from multiple prospective studies, FHI360 Clinical Sciences and Biostatistics Departments led an individual participant data (IPD) meta-analysis of the association between use of hormonal contraception and HIV acquisition. [6] Researchers identified 18 randomized controlled trials of non-contraceptive HIV prevention interventions and cohort studies that contained prospectively-collected data on both hormonal contraceptive use and incident HIV-1 infections [7-24]. With permission of the principal investigators of each study, individual level data from each study were obtained and combined for the Hormonal Contraception and Risk of HIV Acquisition (HC-HIV) individual participant data (IPD) meta-analysis study. Many of these studies also captured information on STI/BV prevalence at baseline and acquisition throughout the course of the study. Although these studies were not specifically identified and combined to investigate STIs/BV, the HC-HIV meta-analysis dataset presents a unique opportunity to explore estimates of STI/BV prevalence and incidence among women in sub-Saharan Africa.

**2. OBJECTIVES**

Using individual level data from the 18 prospective, longitudinal studies included in the HC-HIV meta-analysis dataset, we will estimate the prevalence and incidence of selected STIs/BV among women in sub-Saharan Africa and investigate potential differences by region, population type, and demographic characteristics.

Specifically, we will investigate the following objectives:

1. To evaluate the prevalence of selected STIs (chlamydia, gonorrhea, trichomoniasis, syphilis, and HSV-2) and BV among women in sub-Saharan Africa by region, population type, time period, age, and pregnancy status.
   1. To evaluate the prevalence of co-infections among the STIs/BV
2. To evaluate the incidence of selected STIs (chlamydia, gonorrhea, syphilis, trichomoniasis,and HSV-2) among women in sub-Saharan Africa by region, population type, time period, and age.
   1. To evaluate the incidence of co-infections among the STIs

The term “STIs/BV” may refer to up to 6 conditions: gonorrhea, chlamydia, syphilis, trichomoniasis, HSV-2, and/or BV. For each objective, the precise conditions included were determined by the biological/ epidemiological basis for the particular research question, the availability of STI/BV-specific data at different time points, the validity of combining test results across studies or of calculating incidence for a given condition, and other methodological and biological considerations. See Section 3.3 for more details. Human papillomavirus (HPV) is not included as the majority of studies did not include HPV data.

**3. METHODS**

**3.1. Overview of Studies**

The HC-HIV meta-analysis dataset contains 18 randomized controlled trials of non-contraceptive HIV prevention interventions and cohort studies that contained prospectively-collected data on both hormonal contraceptive use and incident HIV-1 infections. Only studies from sub-Saharan Africa (where most studies have been conducted) were included. The HC-HIV meta-analysis dataset includes data from the 10 studies in the Vaginal Practices Research Partnership (VPRP), a partnership among numerous research groups with longitudinal datasets to investigate a possible association between various vaginal practices and HIV acquisition, and 8 additional studies (Appendix Table 1). All included studies met specific inclusion and exclusion criteria (Appendix Table 2).

The included studies in the HC-HIV meta-analysis dataset were not specifically selected to answer the objectives of this STI/BV prevalence and incidence study and there may be additional studies that could be included (e.g., other cross-sectional or longitudinal studies that include STI/BV data). However, the HC-HIV meta-analysis dataset was previously created in collaboration with study PIs and includes key variables of interest for this study, including STI/BV data, maximizing the utilization of the HC-HIV meta-analysis dataset as well as the efficiency of this analysis. Nonetheless, for the STI/BV analysis, the HC-HIV meta-analysis dataset should be considered a convenience sample of studies.

**3.1.2 Study participants**

The HC-HIV meta-analysis dataset includes study populations where heterosexual transmission is thought to be the predominant mode of HIV transmission. Studies include both women from the general population and groups of women identified at high-risk of HIV infection such as women who engage in transactional sex and HIV-negative women who are part of HIV-discordant couples. Only women from Sub-Saharan Africa are included. If studies included sites outside of Sub-Saharan Africa, only women from the Sub-Saharan African sites were included in the HC-HIV meta-analysis dataset. For incident analyses in the STI/BV meta-analysis, only women in intervention arms which did not include an intervention likely to impact STI incidence will be included. (See Section 3.2)

**3.2. Inclusion and exclusion criteria of studies in the HC-HIV meta-analysis dataset for STI/BV meta-analysis**

The HC-HIV meta-analysis dataset contains data from 18 studies. For each objective, studies in the HC-HIV meta-analysis dataset will be included in the STI/BV analysis based on study design, population, and data availability for each study.

Within each objective, inclusion and exclusion criteria will be applied to each STI/BV separately.

Objective 1: To evaluate prevalence of chlamydia, gonorrhea, trichomoniasis, syphilis, HSV-2, and BV among women in sub-Saharan Africa by region, population type, age, pregnancy status, and time period.

The following types of studies in the HC-HIV meta-analysis dataset will be included:

- Measured the STI/BV at baseline as part of protocol
- Indicates laboratory test used for the diagnosis of the STI/BV
- Includes test result for diagnosis of the STI/BV
- Tested at least 80% of all participants in the study for the STI/BV or tested at least 80% of randomly selected sample of enrolled participants
- Measured important covariates

The following types of studies in the HC-HIV meta-analysis dataset will be excluded:

- Where the study design required the STI/BV diagnosis in question for study inclusion
- If >10% of those tested for the STI/BV had indeterminate test results

Objective 2: To evaluate incidence of chlamydia, gonorrhea, syphilis, trichomoniasis, and HSV-2 among women in sub-Saharan Africa by region, population type, age, pregnancy status, and time period

The following types of studies in the HC-HIV meta-analysis dataset will be included:

- Measured the STI at two or more study visits as part of protocol
  - - Tested for chlamydia, gonorrhea, trichomoniasis, or syphilis at least every 6 months
    - Tested for HSV-2 at least every 12 months or for studies that tested at baseline and end of the study, also had retrospective interim testing at least every 12 months for participants that seroconverted at study end.
- Includes variable to indicate laboratory test used for the diagnosis of the STI
- Includes a population or sub-population that did not receive a STI prevention intervention
  - - - If the intervention in the intervention arm does not have a demonstrated or plausible chance of impact on STI incidence, participants in the intervention arm will be included.
- Protocol indicated testing all participants for STI at specific visits
  - - - Tested at least 80% of enrolled participants for the STI at follow-up or at least 80% of randomly selected participants as per protocol at follow-up
- Measured important covariates

The following types of studies in the HC-HIV meta-analysis dataset will be excluded:

- Where the study design required the STI diagnosis in question for study inclusion
- Where all participants received an STI prevention intervention likely to have an impact on STI incidence
- Where only symptomatic patients were tested on follow-up visits
- If >10% of those tested for the STI had indeterminate test results

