**3.4. Definition of prevalence and incidence**

Prevalent STI/BV infections will be defined by diagnosis at the baseline visit. Infections will be coded as positive, negative, or missing/not classifiable/not collected or asked. Positive syphilis cases will be further categorized based on rapid plasma regain (RPR) titer testing as high titer active infection, low titer infection or unknown RPR titer infection.

Infections defined as:

Chlamydia: Positive: Positive nucleic acid amplification test (NAAT), enzyme immunoassay (EIA), or hybrid capture test

Gonorrhea: Positive: Positive NAAT, or culture

Trichomoniasis: Positive: Positive NAAT, InPouch culture, or wet mount

HSV-2: Positive: Positive type-specific serologic test

BV: Positive: Nugent score (≥7), Ison-Hay grade (≥Grade III), or Amsel criteria (≥ 3 criteria)

Syphilis (see Appendix table 4):

Positive (overall): positive RPR AND positive treponemal test (*Treponema pallidum* hemagglutination assay [TPHA], *Treponema pallidum* particle agglutination assay [TPPA] or Determine TP rapid test)

With subclassification based on RPR titer testing:

Positive, high titer active infection: positive RPR with a titer ≥1:8 AND positive treponemal test

Positive, low titer infection: 1) positive RPR with a titer <1:8 AND positive treponemal test

Positive, unknown RPR titer infection: 1) positive RPR with missing titer AND positive treponemal test

Negative: 1) negative RPR or 2) positive or missing RPR AND negative treponemal test

Missing: 1) positive RPR AND missing treponemal test or 2) missing RPR AND missing or positive treponemal test

For estimation of incident infections, individual study protocols will be reviewed to assess time frames of repeat STI testing, types of laboratory tests used, treatment information for curable STIs. For chlamydia, gonorrhea, trichomoniasis, and HSV-2, incident infection will be defined as the first positive laboratory test following a previously negative result for the infection. For trichomoniasis, incidence estimations will be limited to those studies where *T. vaginalis* testing was done using InPouch or NAAT. For syphilis incidence, using the categories defined above, an incident infection will be defined as:

1. participants who are negative at baseline who are diagnosed at a follow-up visit with a positive infection OR

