| #1 ([name]) | | Yes | | About 70% tested on every FU visit | EIA | Yes | Every FU visit | Culture | Yes | Yes including prevalent and incident HSV2 result | Focus EIA | | Yes | | Yes | Wet mount | Yes | | Some Fup visits | RPR/ TPHA | Yes | Nugent |
| #2 ([name]) | | Yes | | No | Hybrid capture GC/CT DNA assay | Yes | No | Hybrid capture GC/CT DNA assay | No | No | N/A | | Yes | | Some  FU visits | Wet mount | No | | No | N/A | Yes (subset) | Amsel and Nugent |
| #3a/b ([name]) | | Yes | | Every FU visit | NAAT | Yes | Every FU visit | NAAT | Yes | Yes including prevalent and incident HSV2 result | Focus  EIA | | Yes | | Yes | Wet mount | Yes | | Every 6 months | RPR/ TPPA/  TPHA | Yes | Amsel and Nugent |
| #4  ([name]) | | Yes | | >50% tested on FU2 (6M) Fewer tested on other FU visits | PCR | Yes | >50% tested on FU2 (6Mt)  Fewer tested on other FU visits | Culture/  PCR | Yes | Yes, only prevalent HSV2 result | ?? | | Yes | |  | ?? | Yes | |  | RPR/ TPPA/TPHA | Yes | Nugent |
| #5 ([name]) | | Yes | | At 6 and 12 months | PCR | Yes | At 6 and 12 months | PCR | Yes | At baseline and Final visit | IgG Kalon | Yes | | | No | N/A | Yes | | Some  FU visits | RPR/ TPPA | Yes | Nugent |
| #6 ([name]) | | Yes | | At 6, 12, 24 and 30 months | PCR | Yes | At 6, 12, 24 and 30 months | PCR | Yes | Yes  Had to be HSV-2 positive at baseline to join trial | IgG Kalon | Yes | | | At baseline, 6, 12, 24 and 30 months | In pouch and wet mount | Yes | | At baseline, 6, 12, 18, 24 and 30 months | RPR/ TPPA/ | Yes | Nugentand Ison Hay at baseline; Ison Hay at Fup |
| #7a/b ([name], [name]) | | Yes | | Every FU visit | PCR | Yes | Every FU visit | PCR | Yes | Yes including prevalent & incident HSV2 result | FocusELISA | Yes | | | Yes | PCR | Yes | | Final visit only | RPR/ TPHA | Yes, if symptomatic | Amsel |
| #8 ([name], [name]) | | Yes | | Every FU visit |  | Yes | Every FU visit | ?? | All ulcer+, random- | All ulcer+, random- | N/A | Yes | | |  | ?? | Yes | |  | TPPA/TPHA | Yes | Nugent |
| #9 ([name]) | | Yes | | >90% tested on FU2 (6M) & 4 (12M) Few tested on the other visits (max FU4) | ?? | Yes | >90% tested on FU2 (6M) & 4 (12M) Few tested on other visits (max FU4) | ?? | Yes | Yes including prevalent and incident HSV2 result |  | Yes | | |  | ?? | No Lab Form | |  | No Lab Form |  | Yes |

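### For HSV-2 incidence, the Objective 2 testing criteria in 3.2 count baseline-seropositive women, so they do not measure follow-up coverage of the women at risk

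*Protocol*

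**What the plan says.** Section 3.2 lists the study-level criteria for Objective 2 (incidence). One criterion is "Protocol indicated testing all participants for STI at specific visits". Its sub-item sets the coverage threshold: "Tested at least 80% of enrolled participants for the STI at follow-up", or alternatively "at least 80% of randomly selected participants as per protocol at follow-up". The section states that "inclusion and exclusion criteria will be applied to each STI/BV separately", so HSV-2 is judged on its own results, but no HSV-2-specific denominator is given.

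The only HSV-2-specific provision concerns test frequency. Studies that tested at baseline and study end are acceptable if they "also had retrospective interim testing at least every 12 months for participants that seroconverted at study end".

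Section 3.4 measures HSV-2 by type-specific serology. For HSV-2 and three of the curable infections, "incident infection will be defined as the first positive laboratory test following a previously negative result for the infection". Section 3.5 follows each woman to her first diagnosis, the end of the study or her last tested visit.

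**The concern.** Coverage of follow-up testing should be judged on the women who can contribute to the incidence estimate. For HSV-2 under 3.4 these are the women with a negative result, in practice those seronegative at baseline. The criteria in 3.2 count everyone enrolled.

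This can go wrong in two ways. A study that retested all of its seronegative women and nobody else has complete information on HSV-2 incidence, yet may be turned away. A study that retested everyone may clear 80% on the strength of its seropositive women while coverage of the women at risk is poor.

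HSV-2 incidence belongs to a primary objective, and the pool is already limited. In Appendix Table 3, studies 2, 12 and 17 have no HSV-2 follow-up data, study 6 required HSV-2 positivity at entry, and studies 4 and 15 list only prevalent results. That leaves at most 18 − 6 = 12 studies before any stratification by region or population type.

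**Working it through.** The 80% is a fixed criterion, so there is no derived figure to reproduce. The check is what the criterion measures for HSV-2.

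**Inputs**
- Threshold: 80% of enrolled women (3.2).
- p = baseline HSV-2 prevalence. Not in the protocol; treated as an assumption.
- r = share of baseline-seronegative women retested. Not in the protocol; assumed 80% to 100%.
- s = share of baseline-seropositive women retested. Not in the protocol.

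**General form**

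Coverage as the rule counts it = p × s + (1 − p) × r. Coverage of women at risk = r.

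**Case A: only seronegative women are retested (s = 0)**

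Coverage as counted = (1 − p) × r. The 80% clause is met only if p ≤ 1 − 0.80/r.

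| r | Highest p that passes |
|---|---|
| 100% | 1 − 0.80/1.00 = 20.0% |
| 95% | 1 − 0.80/0.95 = 15.8% |
| 90% | 1 − 0.80/0.90 = 11.1% |
| 85% | 1 − 0.80/0.85 = 5.9% |
| 80% | 1 − 0.80/0.80 = 0% |

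Examples at r = 90%: p = 10% gives 0.90 × 0.90 = 81% (passes); p = 20% gives 0.80 × 0.90 = 72% (fails); p = 50% gives 0.50 × 0.90 = 45% (fails). With p = 50% and r = 95% the rule reads 0.50 × 0.95 = 47.5%, while 95% of women at risk were retested.

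The random-sample alternative does not help, because a seronegative subset is chosen by test result. The criterion above the 80% clause, read literally, bars this design whatever p is, since the study's protocol did not plan to test everyone.

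**Case B: every seropositive woman is retested (s = 1)**

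The clause is met when p + (1 − p) × r ≥ 0.80, that is r ≥ (0.80 − p)/(1 − p).

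| Assumed p | Lowest r that passes |
|---|---|
| 30% | 0.50/0.70 = 71.4% |
| 50% | 0.30/0.50 = 60.0% |
| 70% | 0.10/0.30 = 33.3% |

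This is a bound, since it takes complete retesting of seropositive women. If retesting does not depend on serostatus (s = r), coverage as counted equals r and the rule does no harm.

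**With the denominator restricted to baseline-seronegative women**

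Coverage equals r in every case, whatever p and s are.

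**The case against.** The strongest reply is that no affected study is shown. The 18 studies are a closed set, and nothing in Appendix Table 3 says that any of them retested only seronegative women. Typical entries such as "Yes including prevalent and incident HSV2 result" do not say who was retested, and the table is marked as still to be updated. The practical effect could be nil. That stands, and it limits the point to a criterion that is badly specified, with no demonstrated loss.

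A reader might infer more: that the rule admits studies according to their HSV-2 prevalence, keeps the low-prevalence ones and so biases pooled incidence downward. The protocol does not support this. Read literally, the criterion on testing all participants excludes seronegative-only designs at every prevalence, so none is selectively kept. Selection by prevalence arises only if that criterion is read loosely and the 80% clause strictly, and then only among seronegative-only designs. A study that retests everyone at the same rate regardless of serostatus is judged on coverage alone. The step from low prevalence to low incidence also has no figure in the protocol behind it.

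A reader might also see a contradiction with the provision on retrospective testing of seroconverters. There is none: that provision governs how often tests are done and is compatible with testing every woman at study end.

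Two other parts of 3.2 do not resolve the matter. The exclusion "Where the study design required the STI diagnosis in question for study inclusion" removes study 6 but says nothing about who is retested elsewhere. The random-sample route does not fit a subset defined by serostatus.

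Finally, a general change to women at risk would be unclear for the other infections. Under 3.4, a woman with low-titer syphilis at baseline can still become an incident case, and a woman positive for a curable infection can become eligible after a later negative test. This stands, and it confines the fix to HSV-2.

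**Conclusion.** The point holds as a defect in the eligibility criteria for HSV-2 incidence. Both the requirement to test all participants and the 80% clause count women who cannot become incident HSV-2 cases under 3.4. A seronegative-only design is barred by the first criterion read literally and fails the second once baseline prevalence exceeds 1 − 0.80/r: 20% with full retesting of seronegative women, about 11% with 90%. In the other direction, at an assumed 50% prevalence the clause can pass a study with 60% coverage of women at risk.

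The consequences are a possible loss of valid at-risk person-time and a coverage check that does not measure completeness for this outcome. The thresholds follow from the 80% rule and the assumed values of r; the 60% figure also assumes p = 50% and complete retesting of seropositive women. Which studies are affected cannot be told from the protocol, and neither a direction nor a size of bias is established.

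**What to change.** In 3.2, under Objective 2, add an HSV-2-specific version of the two criteria: the study's protocol provided for follow-up testing of every participant who was HSV-2 negative at baseline, and at least 80% of those women, or of a random sample of them, were tested at follow-up. Leave the enrolled denominator unchanged for chlamydia, gonorrhea, trichomoniasis and syphilis. When Appendix Table 3 is updated, record for each study which women were retested for HSV-2.

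The cost is a short wording change and a separate HSV-2 denominator per study, computed from individual data already held. No new data collection is needed.
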